#### 2.1.2. Data collection procedures.

*Data Collection Procedures.* Recruitment focused on youth aged 8–18 years (*M*_age_ =  11.6 years, *SD* =  2.2 years; 62.96% male for included participants) meeting criteria for DMDD (*n* =  38), sub-threshold DMDD (*n* = 10), or ODD (*n* =  6). Some of the participants also had co-occurring anxiety disorder(s) and/or attention-deficit hyperactivity disorder (ADHD).

The means of recruitment and exclusion criteria were the same as for the confirmatory sample, as described in section 2.3.2.

This protocol was carried out from July 2018. Participants were recruited from the Washington, DC, metropolitan area in the context of two ongoing studies (ClinicalTrials.gov Identifiers NCT02531893 and NCT00025935). Recruitment strategies leveraged established relationships with local health care providers and schools and included advertising on Facebook and sending postcards to local households. Outpatients were referred to NIMH.

*Sample size rationale.* Using the preliminary dataset, we aimed to develop classifiers that will be tested in the confirmatory sample. As the presence of severe class imbalance increases the sample size needed for classifier training [28], we ensured that we had enough datapoints to contain at least 100 minority class examples.

*Data splitting.* We formed a training set, stage 1a, from the prompts of a subset consisting of 43 out of 54 participants. The validation set, stage 1b, formed from the prompts of a mutually exclusive subset 11 out of 54 participants, was used to assess model performance. The sample size was thus determined by the size of the existing data and the need to split the data to enable unbiased inference of the classifier performance.

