### 2.4. Results of classifier development on preliminary data

#### 2.4.1. Variable selection.

We considered 23 variables and eliminated six of them by means of a backwards selection algorithm using Bayesian comparison tests [32], as described in section 2.3. The following 17 variables were selected.

The participant’s age and self-reported sex assigned at birth.The participant’s momentary state of feeling: tired, worried, happy, grouchy, angry, frustrated, worried, unhappy, having experienced a change in mood.Whether the day of the week is Sunday, Monday, Tuesday, Wednesday, Saturday, or SundayWhether the time of day is evening.

We excluded the following variables from the model based on the results of variable selection:

Whether the participant has been hungry, or felt giddy.Day of week: Thursday and Friday.Time of day: morning and afternoon.

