#### 2.4.2. Logistic regression.

We determined the optimal number of time lags (1, 2, or 3) to use for logistic regression. The AUC for lag-1 was 0.73, the AUC of lag-2 was 0.78, and the AUC of lag-3 was 0.77. Hence, we selected lag-2 for regularized logistic regression. Detailed results of this analysis are included in S2 Appendix.

The best regularization scheme for logistic regression, as determined using 40-fold cross-validation within the training set, was L2 regularization with C = 0.01. In table 4, we present the model performance for regularized logistic regression, applied to the test examples.

**Table 4 pone.0289235.t004:** Prediction performance of temper outbursts for DMDD, sub-threshold DMDD, and ODD patients in held-out test examples of existing dataset, using regularized logistic regression.

	Precision	Recall	F1-score	Support
No outburst	0.97	0.82	0.89	154
Temper outburst	0.25	0.69	0.37	13

Precision, also called positive predictive value, is defined as the fraction of positive predictions that were true positives (the fraction of times where a temper outburst was endorsed out of the times that the model predicted a temper outburst). Recall, also called sensitivity, is defined as the fraction of positive examples that were predicted to be positive (the fraction of times where the model predicted a temper outburst out of the times in which a temper outburst was endorsed). F1-score is the harmonic mean of precision and recall, given by the formula F1 =  2 *  (precision *  recall)/ (precision +  recall). Support is the total number of test set observations in each category.

Table 5 presents the model weights for logistic regression, as well as Bayesian 95% credible intervals for the variables. We use the Pymc package [35] to implement the Bayesian inference, with N(0,400) prior for the intercept and N(0,0.01) prior (with sigma^2 = 0.01 chosen to match the selected hyperparameter C = 0.01) for each of the non-intercept beta coefficients. For MCMC, we used the NUTS sampler [36] with 10,000 draws and an acceptance target of 0.99.

**Table 5 pone.0289235.t005:** Model weights and intercept for L2-regularized logistic regression, and 95% credible intervals from Bayesian regression.

Variable (lag)	Coefficient	Bayesian 95% credible interval	Variable (lag)	Coefficient	Bayesian 95% credible interval
happy (1)	-0.20	[-0.26, 0.12]	happy (2)	-0.08	[-0.21, 0.18]
unhappy (1)	0.10	[-0.11, 0.27]	unhappy (2)	0.12	[-0.11, 0.27]

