#### 3.2.3. Sample size.

In the confirmatory data set (to be completed by approximately 2027), we plan to collect 20 participants, with an expected total of 300.79 prompts. We determined this prospective sample size based on a power analysis with simulated data.

We simulated data based on a simulation ground truth logistic regression model with L2 penalization, and penalization constant tuned to produce data that would result in a cross-validated accuracy of around 0.40, matching what we saw in the real data. Then, by resampling without replacement participants from the training set, and drawing labels according to the predictions of the simulation ground truth model, we produced synthetic datasets with sample sizes ranging from 1 to 34 participants. For each target sample size, we drew 1000 synthetic data sets of that size, and we assessed the power in terms of the average proportion of coefficients with incorrectly estimated signs using regularized balanced logistic regression. Detailed results are presented in S1 Appendix.

Based on the results of the power analysis, there was a consensus that, when taking into account both the clinical and methodological considerations, the more conservative would be 25 participants, even though a case could be made to justify 15 participants. Our consensus decision is to take the average of these two extremes, and therefore our new plan is to stop collecting participants for this analysis once we have collected 20 participants, which results in around 300.79 prompts on average and has a 31% average sign error for estimating coefficients (Table in S1 Appendix). For this number of prompts, assuming the same proportion of prompts will contain outbursts as in the exploratory sample (10%), we expect to see 30.08 temper outbursts on average.

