i)Checking for distributional shift, by comparing the means and pairwise correlations of all variables between the preliminary dataset vs the test set.ii)Checking for unusual participants, by modeling the joint distribution of the variables between participants as a mixture-of-multinomials model and looking for participants with low likelihood in the mixture-of-multinomials.iii)Checking if any of the variables included in the model are particularly to blame for poor generalization, by fitting models on the training set with one variable removed at a time and seeing if removing any of the variables this way allows for improved performance on the test set.

We believe the results of these analyses would be important in explaining any deviation from our expected results, and helpful to other researchers interested in carrying out similar experiments.

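### Exploratory diagnostic (iii) looks for variables to blame by whether deleting any of 17 improves test performance, but when no variable is at fault at least one deletion raises AUC in essentially every sample

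*Protocol article*

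**What the plan says.** Section 3.3.4 describes a set of diagnostics that are exploratory, optional, and run only if one of three triggers is met. Trigger 1 is an AUC difference of more than 0.05 between the confirmatory and preliminary data.

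The purpose of item (iii) is stated as "Checking if any of the variables included in the model are particularly to blame for poor generalization". The method is to refit on the training set with one variable left out at a time, "seeing if removing any of the variables this way allows for improved performance on the test set". The section adds that the results would matter for explaining departures from expectation and would help other researchers.

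The model being dissected is described in section 2.4. For the predictors: "The following 17 variables were selected". The chosen penalty was "L2 regularization with C = 0.01", with class-balanced weights and two lags. The test set is fixed in section 3.2.3: "we plan to collect 20 participants, with an expected total of 300.79 prompts", and on the 10% outburst rate "we expect to see 30.08 temper outbursts on average".

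**The concern.** The only yardstick in item (iii) is that performance on the test set gets better. Seventeen deletions are tried on one small test set. Each removes a predictor with a small, heavily shrunk weight: in Table 5 every non-intercept coefficient lies within 0.25 of zero and every one of their 95% credible intervals covers zero. Each deletion can therefore be expected to nudge performance slightly up or down, and the best of 17 such nudges will nearly always be upward, whether or not any variable generalises badly.

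At stake is the explanation given if the classifier validates poorly. An EMA item could be reported as the reason, and dropped by others, because of sampling noise.

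**Working it through.** **Inputs.** There are 43 training participants (section 2.1.2: "from the prompts of a subset consisting of 43 out of 54 participants"). The test set has 20 participants and 300.79 prompts, 10% with outbursts (3.2.3). The model is balanced L2 logistic regression with C = 0.01 and two lags (2.4.2), with a preliminary result that "the AUC of lag-2 was 0.78". Coefficients come from Table 5 and item margins from Table 3.

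**1. The plan's own figures reproduce.** Expected outbursts: 300.79 × 0.10 = 30.08. Table 4: recall 9/13 = 0.69; with 27 false positives, precision 9/(9 + 27) = 0.25.

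**2. Number of deletions.** Table 5 has nine items at two lags, plus age, sex, night and five weekdays. That is 9 + 8 = 17 variables and 18 + 8 = 26 coefficients. Removing a variable is taken to mean removing both its lags.

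**3. Rough size.** If each deletion improved performance with probability p, independently, P(at least one improves) = 1 − (1 − p)^17. With p = 0.5 this is 1 − 0.5^17 = 0.99999. It reaches 0.95 already at p = 1 − 0.05^(1/17) = 0.16. The deletions are not independent, so simulation is needed.

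**4. Simulation with no variable at fault.** Training and test youths are drawn from the same model. The full model and the 17 reduced models are fitted on the training data and compared on the test data.

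*Set A* (200 replicates per setting). True coefficients are Table 5 × 2, 3 or 4, plus × 3 with a youth random intercept of SD 1; mean test AUC is 0.66 to 0.80.
- At least one deletion raised AUC in 100% of replicates in all four settings.
- On average 6.7 to 7.6 of the 17 raised it.
- The median best AUC gain was 0.008 to 0.012; the best gain exceeded 0.01 in 39-64% of replicates.
- At least one deletion raised F1 in 95-99%.

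*Set B* (600 to 2000 replicates per setting). Item margins are from Table 3 (the irritable-mood margin stands in for anger, which is not tabulated). Coefficients are Table 5 × 3, 5 or 8. The × 5 settings come closest to the reported AUC:

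| Table 5 × 5 | AUC | Precision | F1 | F2 | Recall |
|---|---|---|---|---|---|
| *No random intercept, mean AUC 0.793* | | | | | |
| P(at least one of 17 improves) | 1.00 | 0.98 | 0.98 | 0.98 | 0.85 |
| Mean number improving | 6.5 | 6.2 | 6.2 | 6.4 | 3.7 |
| 95th percentile of best gain | 0.028 | 0.054 | 0.063 | 0.082 | 0.143 |
| P(best gain > 0.05) | 0.003 | 0.066 | 0.115 | 0.238 | 0.504 |
| *Random intercept SD 1, mean AUC 0.767* | | | | | |
| P(at least one of 17 improves) | 1.00 | 0.98 | 0.98 | 0.98 | 0.86 |
| Mean number improving | 6.9 | 6.3 | 6.4 | 6.6 | 3.7 |
| 95th percentile of best gain | 0.041 | 0.053 | 0.065 | 0.093 | 0.160 |
| P(best gain > 0.05) | 0.025 | 0.058 | 0.134 | 0.284 | 0.538 |

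A further check in set B gave every variable a genuine effect of equal size. Over all set B settings, P(at least one improves) was 99.8-100% for AUC, 97-99% for precision, 96-98% for F1 and F2, and 77-89% for recall. Recall is lower because it moves in steps of about 1/30, so ties are common.

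**5. When the diagnostic would actually run.** Among replicates whose AUC fell more than 0.05 below the setting's mean, P(at least one improves) was 100% for AUC, 96-99% for precision, 97-100% for F1 and F2, and 81-92% for recall.

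**6. How easily trigger 1 fires.** If the true AUC were 0.78, the Hanley-McNeil standard error with 30 outbursts and 271 non-outbursts is about 0.051. Then 0.05/0.051 ≈ 0.98 standard errors, and the AUC would differ from 0.78 by more than 0.05 in about 33% of samples. This assumes independent prompts.

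**The case against.** The strongest reply is that the protocol states no rule that a variable is to blame whenever the best change is positive. It speaks of checking, and the word *particularly* suggests that a variable should stand out; six or seven gains of about 0.01 would not make one stand out. This stands in part: a careful analyst would not blame a variable for a 0.01 gain. But the section gives numerical margins for starting the diagnostics and none for reading item (iii). The only criterion it writes down is improvement, and that criterion has almost no specificity. So this is more than detail left to a fuller document. The metric matters too: a chance best gain above 0.05 is rare for AUC (0.3-2.5%) but occurs in about half of no-fault samples for recall.

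Three stronger readings are tempting, and the documents do not support them.
- *A culprit is always found.* Not on recall alone (77-89%), and not if *particularly* is read as a demand for size.
- *The confirmatory result is compromised.* It is not. Section 3.3.3 bases inference on precision and recall intervals for the pre-fitted model, and item (iii) changes neither the model nor the intervals.
- *The check cannot tell a real fault from none.* This was not tested; every simulated setting had no fault. The size and ranking of the 17 changes may still carry information, and item (i) separately compares means and correlations between the data sets.

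It is also fair to say that unadjusted leave-one-out checks are common in exploratory work. That limits the weight of the point, but does not make improvement alone informative.

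**Conclusion.** The point holds in a limited form. As written, item (iii) takes improvement after deletion as its sign of blame, and that sign appears on AUC in essentially every no-fault sample and in most samples on the other measures. The gains are small on AUC: medians of about 0.01, with a 95th percentile of the largest chance gain of about 0.03 to 0.04 in the settings closest to the plan. An observed AUC gain of 0.02 could easily be over-read.

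The consequence is confined to the explanation offered for a deviation, in an analysis labelled optional and exploratory. The percentages rest on assumed inter-item and within-youth correlations and on scaled-up Table 5 coefficients; the direction of the result held in every setting tried. The change is worth making because it is cheap and because the authors intend the diagnostics to guide others.

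**What to change.** Replace the criterion in item (iii) with wording such as:

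> For each of the 17 deletions we will report the paired change in AUC on the confirmatory set (reduced model minus full model), with an interval from a bootstrap that resamples youths. A variable will be singled out only if its lower limit, adjusted over the 17 deletions by the bootstrap maximum statistic, is above 0. Otherwise we will report that no single variable is identified.

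AUC is the natural metric because trigger 1 already uses it. In no-fault simulations, a youth-level bootstrap with a maximum-statistic limit kept the false-blame rate at about 1-4%. Its power to find a real fault was not assessed.

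The cost is a change of wording and some computing; no new data are needed. The downside is that with 20 youths and about 30 outbursts, unevenly spread between youths (Table 2: mean frequency 0.10, SD 0.16, maximum 0.73), the check will often name no variable. Reporting all 17 changes with their intervals keeps the exploratory information available in that case.

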## 4. Discussion

In this registered protocol, we propose a study for assessing the potential of machine-learning-based methods for enabling multivariate prediction of temper outbursts using ecological momentary assessment data.

Identifying the extent to which temper outbursts can be predicted could be employed in future interventions for pediatric irritability, such as informing pediatric patient, parents and treating clinicians to the child’s clinical status. In future work, EMA reports could also be paired with real-time monitoring of youth’s physiology and behavior to derive a more complete phenotype of irritability and develop precise temporally-informed intervention targets.

One limitation to our study is that all time periods (morning, afternoon, night) are treated equivalently by our modeling approach. However, in practice the delay between night and morning is the longest and, while the delay between afternoon and night is usually longer than the delay between morning and afternoon, there is some variability as participants are free to choose when to complete the prompt within the allowed window. Therefore, it is plausible that there could be differences between the three times of day in terms of the optimal prediction rule. However, when we attempted to fit time-of-day-specific prediction models, we saw no statistically significant difference in the performance of time-of-day specific models and the model that we developed based on all times of day (Table A in S2 Appendix). Yet, given more data it might be possible to develop time-of-day-specific classifiers for differing times of day that would outperform a time-of-day-general classifier.

There are two additional major limitations to this proposed study. Firstly, the sample will be nonrepresentative, as the study consists of individuals who choose to participate in NIMH studies. To mitigate the bias due to the nonrepresentative study population, we will recruit across the community. Furthermore, some biases may be due to participation being potentially limited by factors that facilitate remote research compliance. Reasons for lack of participation include finding the task to be boring or annoying, or conflict between the task and existing activities. To increase compliance, we will allow participants to adjust the scheduling of the responses within 3-hour intervals for morning, noon, and evening, and randomized the timing of the prompts within the selected 60-minute interval for each time period. However, we recognize that the freedom to select the response period may lead to additional bias due to possible confounding between preferences for timing windows and measured behavior.
